**Methods:**

This randomized double-blind controlled study aims to recruit a total of 100 participants, consisting of 50 children aged 3–7 years with an EBP measure rated above the clinically significant range (T-score ≥ 60) (Eyberg Child Behavior Inventory-ECBI; Eyberg & Pincus, 1999) and their parents who are at least 18 years old. Participants are randomly assigned to the artificial intelligence-PCIT group (AI-PCIT) or the PCIT-sham biometric group. Outcome parameters include weekly ECBI and Pediatric Sleep Questionnaire (PSQ) as well as Child Behavior Checklist (CBCL) obtained weeks 1, 6, and 12 of the study. Two smartphone applications (Garmin connect and mEMA) and a wearable Garmin smartwatch are used collect the data to monitor step count, sleep, heart rate, and activity intensity. In the AI-PCIT group, the mEMA application will allow for the ecological momentary assessment (EMA) and will send behavioral alerts to the parent.

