### Objectives

The overall objectives of this AI-PCIT treatment clinical trial are to evaluate feasibility of the use of wearables such smartwatches: in children aged 3–7 years with emotional behavioral problems (EBP). We hypothesize that children with EBP undergoing PCIT will adhere to and tolerate wearables (e.g., Garmin vivosmart4 smartwatch) by having at least 70% of enrolled patients being able to wear it 70% of their treatment period. This will be monitored by checking sleep, heart rate, and intensity of data obtained from Garmin watches. The study will also evaluate the effectiveness of AI-PCIT by comparing weekly behavioral treatment outcomes as compared with control group over a 12-week period. The study will also serve to track indirect behavioral measures on smartwatches (i.e., measurements of heart rate, intensity of activity) from young patients as compared to parental rating scales of ECBI (obtained weekly). These measures can then be used for target engagement biomarkers in future interventional trials. Finally, we will also collect whole blood from both child and parent to investigate exploratory analyses on biomarkers (e.g., C-reactive protein, metabolomics, exposomics) of response to PCIT.

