## Methods

Our clinical trial is examining the AI-PCIT for treatment of externalizing behavioral problems in young children. Participants are recruited from Young Child Behavioral Clinic (YCBC) at Mayo Clinic in Rochester, MN, USA, and through advertisements at local pediatrics and family medicine clinics. Interested participants are initially provided information about the study and are scheduled for a consult in the Young Child Behavioral Clinic. The overall recruitment goal for the trial is *N* = 50 participants between ages of 3–7 years whose measure of EBP rated above the clinically significant range (T-score ≥ 60) (Eyberg Child Behavior Inventory-ECBI; Eyberg & Pincus, 1999) [3]. Participants are randomly assigned to AI-PCIT group or PCIT-sham biometric group. Each child is recruited with their parents who are at least 18 years old for a total recruitment of 100 participants. Participants are children aged 3–7 years old. They are of any gender, race, or ethnicity recruited from outpatient or inpatient care. Inclusion criteria include the patients’ ability to provide developmentally appropriate informed assent and legal guardians that are able to provide informed consent. Furthermore, the patient’s EBP severity must be rated above the clinically significant range (≥ 120; T-score ≥ 60) (Eyberg Child Behavior Inventory-ECBI; Eyberg & Pincus, 1999) [3]. The need for more intensive behavioral treatments such as an ER visit or hospitalization for behavioral dyscontrol will not be exclusionary or exit criteria. Participants must be fluent in the English language, have verbal abilities, and have the competency to consent based on ability to provide a spontaneous narrative description of the key elements of the study. Participants also require at least one smartphone and Internet access. Exclusion criteria for the PISTACHIo clinical trial include individuals who are unable to speak and understand English; patients who refuse or withdraw their consent, or those who are unable or unwilling to adhere to study procedures; and patients who do not have a smartphone and access to Internet connection. The study has the approval of the local institutional review board for human subject research protection (Mayo Clinic, Rochester, MN, USA).

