### Study procedures

The PISTACHIo clinical trial utilizes a randomized, double blind, design to compare the active PCIT-AI group and PCIT-sham (treatment as usual) group. The child and primary caretaker are fitted with Garmin watches that are required to be worn for a minimum of 70% of the days during their 12 weeks of treatment. In addition to this, we require the participants to wear the watch for at least 70% of every 24 h per the principal investigator’s discretion. Families are scheduled for PCIT treatment with PCIT-certified therapist in the Young Child Behavioral Clinic. Before the first PCIT treatment session, all participants are randomized into an active versus sham arm of the study. This is done by using a computer-generated list based on a stratified randomization scheme and using a permuted block method with a random number generator. The research assistant, research coordinator, and computer engineer who monitors Garmin apps are the only team members aware of which group the participant belongs to (active vs sham) [20]. Study investigators, clinical/cognitive raters, and participants are blind to the treatment condition. Parents in the AI-PCIT group are receiving targeted messages that instruct them on how to de-escalate their child when the Garmin device recognizes vital signs associated with a child’s tantrum. Parents in the PCIT-sham group receive random messages throughout the day with various relaxation strategies such as reminders to practice deep breathing with their child. The treatment is overseen by board-certified child and adolescent psychiatrist who is a Within-Agency PCIT Trainer.

Any participants withdrawn from the study if they were non-adherent to study procedures or met exclusion criteria at any point after the consent will not be replaced, and their data will not be used for analysis. Additionally, broken watches will be replaced, and therefore, the participant will not be excluded from the study.

The ongoing clinical trial study protocol conforms to the International Consolidated Standards of Reporting Trials (CONSORT) guidelines and is registered on Oct 14, 2021, in clinicaltrials.gov (ID: NCT05077722), an international clinical trial registry. See Fig. 1 depicting the PISTACHIo study workflow and timing for study procedures.

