### Proposed analysis

This study is an exploratory clinical trial with the broad goals of demonstrating feasibility, producing pilot data, generating validate effect sizes, and informing future larger, multicenter trials. The level of significance will be set at *α* = 0.05 (two tailed), and to address multiple testing (where applicable), *p*-values will be adjusted using the false discovery rate. We estimated the sample size for this pilot study based on the hypothesis examining clinical outcome (ECBI) between the PCIT-AI group and PCIT-sham group (hypothesis 2a). We anticipate that a sample size of 50 participants per group (*N* = 100) achieves 70% power, at a 0.05 alpha level (two tailed) to detect an odds ratio of 2.0 favoring PCIT-AI with the proposed randomized design. To evaluate feasibility of the use of Garmin wearables, we will use descriptive statistics assessing the frequency of Garmin use in participants (70% or greater is defined as success for this hypothesis). A linear mixed model analysis of repeated measures will be used to evaluate the interaction effects of type of PCIT (AI informed or AI sham), time, and ECBI scores. A separate linear mixed model analysis will be used to evaluate the interaction effects of PCIT type (AI informed or AI sham), time, and PSQ scores with ECBI scores as a covariate. To evaluate concordance of sleep cycle data from children aged 3–7 as compared to parental rating scales of PSQ, we will use Spearman correlation coefficients and mixed linear regression models. Separate Spearman correlations and a mixed linear regression model will examine the relationship between biometric data from smartwatches (heart rate and movement) with weekly ECBI reports. Partial least-square regression networks will be used to derive multi-omic integration networks, and Spearman correlation will then be used to associate omics with physiological measures from smartwatches.

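### The PSQ treatment model takes ECBI scores as a covariate without limiting them to baseline; weekly ECBI would block part of the randomised effect on sleep

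*Protocol article*

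**What the plan says.** The Proposed analysis section sets out two linear mixed models in consecutive sentences. The first is meant "to evaluate the interaction effects of type of PCIT (AI informed or AI sham), time, and ECBI scores", so ECBI is there the repeated outcome. The second covers PCIT type, "time, and PSQ scores with ECBI scores as a covariate". Neither sentence gives the covariate a time point, and no mediation or direct-effect aim is attached to the second model.

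Other places fix what ECBI is and when it is measured:

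- **Outcome.** The sample size rests on the "hypothesis examining clinical outcome (ECBI) between the PCIT-AI group and PCIT-sham group", labelled hypothesis 2a.
- **Frequency.** The Abstract (Methods) opens its outcome list with "Outcome parameters include weekly ECBI and Pediatric Sleep Questionnaire (PSQ", the abbreviation closing the phrase. The Objectives section likewise refers to "parental rating scales of ECBI (obtained weekly", and describes the effectiveness aim as "comparing weekly behavioral treatment outcomes as compared with control group over a 12-week period".
- **Randomisation.** Study procedures states: "Before the first PCIT treatment session, all participants are randomized into an active versus sham arm of the study".
- **Entry value.** Under Methods, eligibility requires that "the patient’s EBP severity must be rated above the clinically significant range", so every child has an ECBI score from before treatment.

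**The concern.** A randomised comparison is protected because allocation is independent of everything measured before it. That protection is lost when the model conditions on something measured afterwards that treatment can alter. Weekly ECBI is such a variable. The active messages coach parents to de-escalate tantrums, and ECBI is the outcome on which the trial hopes to show a difference.

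Two things can go wrong if weekly ECBI enters the PSQ model:

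1. **Blocked pathway.** If calmer behaviour improves sleep, that part of the treatment effect is absorbed by the ECBI coefficient and disappears from the group-by-time term.
2. **Shared error.** Both scales are parent-rated, with one primary caregiver per child. If the two scores share rating error or family circumstances, holding ECBI fixed can produce a difference in PSQ between arms where none exists.

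The trial is meant to supply effect sizes for larger multicentre studies. A PSQ estimate stripped of its behavioural pathway would be carried into that planning, and the distortion grows with the effect on ECBI.

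**Working it through.** **Step 1. Which ECBI is meant?** The plan gives no figure to reproduce here, so the first step is textual.

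- For the weekly reading: the same two words, ECBI scores, denote the repeated outcome one sentence earlier; ECBI is collected weekly; no baseline qualifier appears.
- For the entry reading: an entry score exists, and a later sentence of the same section, on smartwatch data, does add the word weekly to ECBI.

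The weekly reading is likelier but not certain.

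**Step 2. What the adjusted term estimates.** In the linear case

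adjusted PSQ effect ≈ total PSQ effect − (PSQ-on-ECBI slope × ECBI effect).

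The documents give no slope and no ECBI effect in SD units, so both are assumptions. The one effect the plan states, an odds ratio of 2.0, converts on the logistic scale to ln(2) × √3/π = 0.38 SD. The amount removed from the PSQ effect is then:

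| Slope | ECBI effect 0 | 0.38 SD | 0.5 SD |
|---|---|---|---|
| 0 | 0 | 0 | 0 |
| 0.25 | 0 | 0.10 | 0.13 |
| 0.5 | 0 | 0.19 | 0.25 |

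**Step 3. Blocking, checked in the planned type of model.** Mixed models were simulated with 4,000 children, weeks 0 to 12, and random intercept and slope. The ECBI effect at week 12 was −0.5. Entries are the estimated group-by-time effect on PSQ at week 12, in SD-like units.

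| Assumed truth | True total | No ECBI | Baseline ECBI | Weekly ECBI |
|---|---|---|---|---|
| Slope 0.5, no direct effect | −0.25 | −0.257 | −0.257 | +0.007 |
| Slope 0.5, direct effect −0.25 | −0.50 | −0.515 | −0.515 | −0.250 |

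Weekly ECBI removes all of the effect in the first case and half in the second. Baseline ECBI leaves the estimate unchanged.

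**Step 4. Shared error, no true PSQ effect.** Assume shared variance 0.5 and an ECBI effect of −0.5 SD. The formula for a single visit gives 0 − 0.5 × (−0.5) = +0.25 SD, which is apparent harm if higher scores are worse on both scales. In a random-intercept model over repeated visits the result depends on the kind of error:

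| Shared error | Visits | Spurious group-by-time difference (SD) |
|---|---|---|
| Stable rater or family factor | 13 weekly | 0.03 to 0.04 |
| Stable rater or family factor | 3 | about 0.17 |
| Occasion-specific | 13 weekly | about 0.25 to 0.28 |

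With many visits the random intercept absorbs most of a stable factor. It cannot absorb error that is new at each occasion.

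**The case against.** **The text does not say weekly.** The covariate carries no time point, an entry score exists for every child, and the section uses the word weekly elsewhere when it means it. A condensed article may also leave such detail to a fuller document. This stands in part. It lowers confidence, and a reader who infers that the protocol definitely commits to a time-varying covariate goes further than the words allow. It does not remove the point: the article does specify this model, and the natural reading of its wording is the harmful one.

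**A direct effect may be the target.** Asking whether sleep differs by arm beyond behaviour change is a legitimate question, and the Objectives section states no hypothesis about a total effect on sleep. But the Abstract and the Clinical significance section list PSQ among the outcome measures, and no mediation aim is stated. This mitigates and does not rebut.

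**False harm is overstated.** A reader might infer that the planned model would show spurious harm of about 0.25 SD because the same parent rates both scales. The documents do not support that. Rater and family factors are largely stable, and with weekly scores a stable factor leaves only about 0.04 SD. The larger figure needs occasion-specific error or few visits. This objection stands.

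**The consequence is limited.** The trial is exploratory, PSQ is neither the feasibility measure nor the basis of the sample size, and the ECBI model is untouched. This also stands, and it bounds the severity.

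**Conclusion.** The point holds, with moderate confidence. As worded, the PSQ model admits, and more likely than not means, adjustment for an outcome measured after randomisation. On that reading its group-by-time term does not estimate the randomised effect on PSQ.

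The main damage is blocking. With an assumed ECBI effect of 0.5 SD and slope of 0.5, a PSQ effect of 0.25 SD that acts through behaviour is estimated as about 0. Spurious difference from shared parent rating is a lesser and conditional risk. Neither distortion arises if treatment leaves ECBI unchanged or if the two scores are unrelated. If only the entry ECBI is meant, no distortion arises either and the defect is one missing word. All sizes rest on assumed values, not on figures in the article.

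This should be corrected, but it concerns a secondary, exploratory outcome and does not touch the main ECBI comparison.

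**What to change.** State that the PSQ treatment comparison adjusts only for pre-randomisation values: baseline PSQ and, if wanted, the ECBI score already obtained for eligibility. State also that ECBI scores collected after randomisation are not covariates in that comparison. If the link between behaviour and sleep is of interest, report a model with weekly ECBI separately, labelled as an exploratory association or mediation analysis. If entry ECBI was meant all along, adding the word baseline is enough.

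The cost is one sentence in the analysis section. No new data, visits or participants are needed.

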## Discussion

Currently, there are no AI-augmented treatments for young children with EBP. PCIT is an evidence-based behavioral treatment for 3–7 years old with EBP supported by numerous meta-analyses studies [12, 34, 35]. Attrition rates in PCIT are high and can reach 25 to 69% depending on the study [13, 36]. Factors such as education, income, family employment, and parents’ engagement have been cited as main reasons for attrition [37].

Our study is first to offer AI-augmented PCIT treatment for young children with EBP which will allow for improved engagement of families. The main goal of PCIT is to strengthen the relationship between the parent and child. With the use of our Garmin technology, we can augment that goal by sending targeted messages to parents in critical moments when their child needs help. What is particularly innovative about our project is that the chosen smartwatch does not require the young child to spend time in front of a screen or to interact with an app, both situations that many parents are opposed to for children of this age range. Instead, it helps parents to remember important therapy techniques during real-world parent/child interactions which can be vital learning opportunities for the dyad.

Our study additionally provides us with a valuable environment to test the relationship between multi-omic associations of disruptive behaviors in a parent–child dyad and associations with physiological smartwatch measures. This has never been studied in children with EBP.

It is important to note that data privacy is a significant concern in mobile health, particularly in the research area. As a procedure at enrollment, the study team disengages location, calendar, contacts, social media, and microphone settings on the Garmin Connect and mEMA applications. However, the study will not stop participants from using their discretion to change these settings should they choose to utilize additional features commodity smartwatches provide. Additionally, all self-reported assessments through the mEMA application are deidentified as the connection between the application, and the Ilumivu website is done through a randomly generated code accessed by IRB-approved study personnel.

Another important ethical consideration is related to the burden of the mEMA app. Generally, EMA methods require time commitment on behalf of the patients, and in our study, it relies on daily assessments done on the mEMA app. This could affect the adherence of the participants. However, receiving notifications as daily reminders and reminding patients about the daily assessments every week during therapy should improve compliance. Additionally, participants will receive weekly reimbursement for completing the assessments and therapy sessions which should also cause a significant increment in compliance. The mEMA application is easy to use with a simple interface that directly takes the participants to the assessments. Moreover, because EMA relies on recording participants’ continuous experiences, this may be more invasive than having the participant answers a retrospective questionnaire. This should prompt the consideration of the risk of intrusiveness into the daily life of the patients on one hand and the inconvenience of receiving requests at inopportune times.

The benefit of using commodity smartwatches to predict tantrums lies in the ubiquity of these devices. Approximately 3 in 10 children wear smartwatches, and that number is expected to grow. Valid physiologic smartwatch biomarkers will have a number of clinical and research implications. Smartwatch biomarkers will be readily scalable for widespread clinical practice. Smartwatch physiologic biomarkers will revolutionize clinical trial research in children and adolescents [38–41]. The research team has active plans for future studies to develop diagnostic biosignatures and interventional trials for children with mental health disorders. These future clinical trials through applications to the National Institutes of Health will span novel behavioral interventions, pharmacological agents, and technology-based interventions informed by FDA guidance on “real-world evidence” [38, 42–45].

## Conclusion

The PISTACHIo study is positioned to determine whether AI-PCIT treatment is a superior treatment of EBP. For the first time, we will be able to determine tolerability of smartwatches in children aged 3–7 with EBP. Given the novelty of the study in engaging with parents and children through smartwatches and mobile applications, we anticipate the following findings that will guide future digital health interventions for families with children diagnosed with disruptive behavior. First, we expect that very young children with severe behavioral and compliance issues will want to wear, and tolerate wearing, smartwatches for 12 weeks of the study. Second, we expect that patients commit to daily, albeit brief, engagement with the app and weekly therapy sessions. This intense schedule may limit our ability to recruit to our trial. On the other hand, patients will be encouraged to communicate with research staff in case of issues, and children will be offered toys for their willingness to wear their watch every week. This may cause some unintended therapeutic effects. Typically, in PCIT, children are not provided toys on a weekly basis.

### Clinical significance

The current study aims to develop an innovative wearable tracking protocol that will use AI technology. This research has the potential to begin critical work on innovative assessment strategies for the youngest patients struggling with significant emotional-behavioral issues. Smartwatch data and artificial intelligence approaches will have enhanced temporal resolution compared to standard assessments, again proving the importance of this work. This would be the first time such a treatment model is used in children below 8 years of age, and, as such, our proposal is innovative in a number of ways. These innovations will facilitate the following: (1) collection of more objective and longitudinal behavioral measures; (2) assessments of standard clinical outcome measures such as the ECBI, PSQ, and the rate of tantrum events/duration everyday activities; (3) identification of early opportunities for reinforcing positive behavior that is child-specific; and (4) an understanding of the origins behind childhood disruptive behavior. Artificial intelligence methods such as reinforcement learning and probabilistic graphical models will be used to develop methods for data analysis. These methods are suitable for longitudinal data such as the data gathered in this trial. Information collected from the PISTACHIo research study can incorporate time-sensitive changes as well as physician knowledge to make childhood prognoses detailed and interpretable.

## Data Availability

The datasets used and analyzed during the current study are available from the corresponding author on reasonable request.
